##### Process evaluation

Process evaluation will be guided by the implementation component of EPIS framework and the CFIR. The CFIR has five constructs: intervention characteristics, outer setting, inner setting, characteristics of individuals, and process. These constructs serve as a foundation to explore the factors affecting implementation process, including barriers and facilitators of service delivery [33]. Accordingly, the project advisory group will evaluate the compliance of implementing agencies and sites with the multi-component interventions included in the model of care. Participating sites will also assess whether the required structural and system changes have been implemented and whether healthcare professionals and other implementing staff have adopted the intended behavioural changes. These evaluations will be guided by the frameworks described above. Compliance monitoring at each site will be conducted by selected staff using a structured checklist, with results reported to the project advisory group on a quarterly basis.

If significant non-compliance with the implementation protocols is observed, a re-assessment will be conducted to evaluate the fidelity and acceptance of the model of care. Accordingly, in-depth interviews will be conducted with the health care professionals and other implementing agencies to better understand the issues they faced, and the challenges experienced during implementation of the multi-packaged interventions. These results of the findings will be utilized to make contextual adjustments on the provided list of interventions in the model of care or provide additional capacity building trainings. As such, the multi-packaged interventions will be either adapted as per the challenges noted or co-developed as per the site needs. Otherwise, retraining will be provided if retraining alone is sufficient. Then, a final assessment will be conducted to assess the implementation process and clinical outcomes of implementing the multi-packaged model of care in enhancing access to and utilization of health services for hypertension and diabetes mellitus screening and initiation of treatment among CALD communities [34] (Table 1).

**Table 1 Tab1:**
[figure not shown]
Model co-development, preparation and implementation considerations with proposed implementation outcomes, from complementary frameworks perspective

### Phase IV: Post-intervention phase

This phase will involve collecting data in order to evaluate the implementation outcomes of the multi-packaged model of care. The effectiveness of these complex interventions in their specific settings will be evaluated by the different stakeholders involved in the implementation process. This will include assessing the implementation process outcomes and impacts of the model of care in enhancing access to and utilization hypertension and/or diabetes screening services among CALD communities. For this reason, we will collect quantitative data to measure model implementation impacts in terms of access enhancement, utilization rate and other clinical outcomes. In addition, we will be conducting qualitative interviews with the different stakeholders and collaborators in order to evaluate their thoughts about the feasibility, sustainability and potential long-term impacts of the implemented multi-packaged model of care (Fig. 2).

**Fig. 2 Fig2:**
[figure not shown]
Phase-wise research strategy, model co-development and implementation process to enhance access to and utilization of hypertension and/or diabetes screening services among CALD communities in Australia

### Outcomes of model implementation

The primary model implementation impact outcome is “Reach”, or the proportion of eligible CALD adults completing hypertension and/or diabetes screening. The primary implementation process outcomes are acceptability, appropriateness, and feasibility of the model of care, measured at the site and stakeholder level. Secondary outcomes include follow-up completion, treatment initiation, clinical control (BP and glycemia), intervention fidelity, program cost, and sustainability. Baseline measurements will be collected prior to implementation, with follow-up assessments occurring at 6 to 12 months post-implementation depending on the specific outcome (See Supplementary File 1). The sustainment component of EPIS framework and the RE-AIM evaluation framework will be utilized to guide assessment of these implementation outcomes related with implementation of the multi-packaged model of care. The RE-AIM framework is a widely used planning and evaluation tool in public health that helps assess the impact and scalability of health interventions across five key dimensions: Reach (the extent to which the target population participates), Effectiveness (the impact on important outcomes), Adoption (the extent to which settings and staff adopt the intervention), Implementation (how well the intervention is delivered as intended), and Maintenance (the extent to which a program is sustained over time) [35]. Originally developed to bridge the gap between research and real-world application, RE-AIM guides both the design and evaluation of programs to ensure they are not only effective in controlled trials but also practical and sustainable in everyday settings. However, some of the implementation outcomes in this study, specifically acceptability, appropriateness, feasibility, fidelity and cost are not native RE-AIM domains. These outcomes are intentionally drawn from Proctor et al.’s taxonomy to complement RE‑AIM’s implementation dimension with complementary measures being mapped pragmatically across the two frameworks [35, 36]. Reach will be calculated as the number screened divided by the number invited within each site and period based on community registries and screening logs. In addition, individuals who screen positive during each measurement period will form a nested cohort for follow up, and these clinical pathway outcomes will be summarised and analysed as site period proportions to remain consistent with the repeated cross-sectional design.

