
#### Expected outcomes of Phase II

Co-development of a culturally responsive, community based, multi-packaged model of care to enhance access to and utilization of health services for hypertension and diabetes mellitus screening, and initiation of treatment for those diagnosed among CALD communities in Brisbane city, Australia. For instance, making services periodically available and accessible around faith-based settings, doing health promotions through community leaders and health professional facilitators, registry of target population and provision of services can potentially enhance access to and utilization of health services for hypertension and diabetes mellitus screening, and initiation of treatment for those diagnosed among CALD communities. Previous research in this area has demonstrated success in early detection and treatment for such disorders [30–32].

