Once the pre-implementation preparation phase is completed, the actual model implementation phase will be started in the selected faith-based community settings in collaboration with different health care providers in the city. These collaborating health facilities will be tasked to work with the faith-based CALD community leaders on ways of enhancing access to and utilization of health services for hypertension and diabetes mellitus screening, and initiation of treatment for those diagnosed. For the pilot testing purpose, the implementation process will focus on involving adults aged 40 years and above. Accordingly, we will be communicating with those religious organizations for their consent and cooperation once the ethical approval process is finalized and permissions are obtained from other concerned bodies in the health system. Then, people from these communities who were born overseas and are 40 years or older will be registered and invited for the service in collaboration with the project implementing health facilities. Additional key activities in this phase includes executing the plan, monitoring fidelity and outcomes through data collection, and using feedback for continuous improvement. Essential support systems such as coaching, supervision, and resource provision will be facilitated by the project advisory group in collaboration with the implementing site managers/coordinators during this phase, to sustain momentum and address challenges. Flexibility and responsiveness to real-time feedback will be emphasized to ensure that the multi-packaged interventions are delivered effectively, and adjustments are made when needed.

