
### Proposed tools for measuring implementation outcomes

There are various tools that have been utilized to assess various implementation outcomes across the literature. We will be using different adapted tools including the Acceptability of Intervention Measure (AIM), Intervention Appropriateness Measure (IAM), and Feasibility of Intervention Measure (FIM), psychometrically validated tools developed to assess key early-stage implementation outcomes. Each of these instruments consist of four items, rated on a five-point Likert scale from “completely disagree” to “completely agree.” The AIM captures the degree to which stakeholders find an intervention agreeable or satisfactory, making it a useful measure of perceived acceptability. The IAM evaluates whether an intervention is perceived as a good fit or relevant for a given context or problem, thereby assessing its appropriateness. The FIM measures the perceived practicality and ease with which an intervention can be successfully implemented in a specific setting. These tools are designed for ease of use, brevity, and reliability, making them highly suitable for integration into implementation research and practice across diverse settings [37]. In addition, other tools will be utilized depending on the expected outcome measures including the Clinical Sustainability Assessment Tool (CSAT), Short Form, and the Program Sustainability Assessment Tool (PSAT), Short Form, for model implementation sustainability assessment (Table 2).

**Table 2 Tab2:** Implementation outcomes and proposed assessment tools for the model of care

	Constructs	Assessment tools/Measures	Source of data	Method
RE‑AIM Implementation Evaluation Framework with Proctor et al. style implementation outcomes	Reach	Participation rate: % of individuals invited who actually undergo screening for the target NCDs.	Registry lists and clinical records	-
	Effectiveness	Follow-up rate: % of screen-positive individuals who receive timely confirmatory diagnosis and/or treatment.	Clinical records	-
		Proportion of people with controlled hypertension and diabetes among those diagnosed.	Clinical records	-
				-
	Adoption	Proportion of implementing agents/staffs that deliver model of care components.	Clinical records	-
	Implementation			
	✓ Acceptability	Acceptability of Intervention Measure (AIM) 4-items [37].	Implementing site staff members	Survey

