### Data analysis plan for the main model

The Difference in Differences approach will be used to compare changes in hypertension and diabetes screening uptake between intervention and control sites over time with a repeated cross-sectional design. A Generalized Estimating Equations model will be utilized as the primary analysis method with site clustered robust standard errors and an appropriate small sample correction to account for the limited number of clusters. In addition, a generalized linear mixed model with a site level random intercept will be used as a sensitivity analysis. Key participant characteristics including age, sex, region of birth, education, primary language, and baseline comorbidities will be included as covariates. Results will be presented as adjusted marginal effects with 95% confidence intervals. Baseline equivalence between intervention and control sites will be examined using standardized mean differences, and any identified imbalances will be controlled for in the modelling. The parallel trends assumption will be assessed indirectly through these baseline comparisons and sensitivity analyses as only one pre intervention time point is available. For secondary outcomes, follow up completion, treatment initiation, and clinical control will be derived from the nested cohort of screen positive individuals and will be summarised and analysed as site period proportions. Missing data will be handled using multiple imputation with additional sensitivity analyses to evaluate the robustness of findings. If individual level data are pooled across sites with fixed per site samples, design weights proportional to the site population of eligible invitees will be used to account for unequal selection probabilities (See Supplementary File 1).

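### The primary outcome Reach has two denominators, and the one used to calculate it depends on the intervention and is described for only one of the four Difference-in-Differences cells

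*Protocol article*

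**What the plan says.** Under Outcomes of model implementation, Reach is named the primary impact outcome and described as "the proportion of eligible CALD adults completing hypertension and/or diabetes screening". Later in the same section the calculation rule is: "Reach will be calculated as the number screened divided by the number invited within each site and period based on community registries and screening logs". Table 2, under Proposed tools for measuring implementation outcomes, follows the second form. It gives a participation rate, the percentage "of individuals invited who actually undergo screening for the target NCDs", and lists registry lists and clinical records as the source.

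The one place where individuals are said to be registered and invited to screening is the Phase III section. Once implementation has begun in the selected faith-based settings, "people from these communities who were born overseas and are 40 years or older will be registered and invited for the service", jointly with the implementing health facilities. Expected outcomes of Phase II offers, as an example of what the model might contain, that a "registry of target population and provision of services can potentially enhance access to and utilization of health services".

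The design is two-period Difference-in-Differences with repeated cross-sections, with six intervention and six control sites. Baseline is measured before implementation. The Data analysis plan for the main model will "compare changes in hypertension and diabetes screening uptake between intervention and control sites over time". If data are pooled with fixed samples per site, it weights by each site's population of eligible invitees.

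**The concern.** A Difference-in-Differences estimate subtracts one before-after change from another. It can be read as an effect only if the same quantity is measured in the same way in all four cells. Here the denominator of the primary outcome counts people reached by an activity that the protocol places inside implementation. The comparison could then reflect who was invited and logged, rather than whether more eligible adults were screened.

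The two denominators also answer different questions. Screened over eligible measures population coverage. Screened over invited measures response to an invitation. A team following the article could defend either as the primary result.

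**Working it through.** **The plan's own figure.** The sample size compares 50% with 70% at 80% power and 5% significance (two-sided assumed). The unpooled normal approximation gives (1.960 + 0.842)² × (0.25 + 0.21) / 0.20² = 90.3, so 91 per group and 182 in total, as stated. The design effect is 1 + 99 × 0.02 = 2.98, and 182 × 2.98 = 542.4, so 543, as stated. The arithmetic stands. The 50%, however, is derived from awareness among people with hypertension. It is not a ratio of screened to invited, so it does not show what that ratio would be at baseline.

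**The two denominators.** Let q be the share of eligible adults who are invited, and u the share of invitees who are screened. Screened over invited is u. If only invitees' screens are counted, screened over eligible is q × u. If the uninvited are also screened elsewhere at rate b, it is q × u + (1 − q) × b. Take u = 0.70 (the plan's target) and b = 0.50 (its assumed baseline). The article gives no value for q, so the range below is an assumption:

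| q (assumed) | Screened / invited | Screened / eligible, invitees only | Screened / eligible, with 50% of uninvited screened elsewhere |
|---|---|---|---|
| 0.3 | 0.70 | 0.21 | 0.56 |
| 0.5 | 0.70 | 0.35 | 0.60 |
| 0.7 | 0.70 | 0.49 | 0.64 |
| 0.9 | 0.70 | 0.63 | 0.68 |
| 1.0 | 0.70 | 0.70 | 0.70 |

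With these rates the definitions coincide only at q = 1. The table shows how they part below that. It does not predict q.

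**The four cells.**

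| Cell | Invitation step described? |
|---|---|
| Intervention sites, baseline | No; baseline precedes implementation |
| Intervention sites, follow-up | Yes; Phase III section |
| Control sites, baseline | No |
| Control sites, follow-up | No; the control group is by design not affected by the intervention |

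**What follows for the three undescribed cells.** There are two possibilities.

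1. They issue no invitations. The number invited is then zero, and the stated ratio is undefined.
2. They register, invite and screen people so that the ratio can be formed. Control sites, and intervention sites before the start, then receive part of what is being tested.

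In neither case does the contrast compare like with like.

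**Data sources.** The calculation rule relies on screening logs, while Table 2 relies on clinical records. A log kept by the programme and a clinical record need not capture the same screens, particularly those done in usual care. The two statements need to be aligned.

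**The case against.** The strongest reply is that the article plans for Reach in every cell. It says the ratio is formed for each site and period, expects people to screen positive in each measurement period, and refers to eligible invitees by site. Nowhere does it say that baseline or control sites lack registries or invitations. A reader might infer that Reach cannot be formed in three of the four cells, but the text does not support that. It is silent on how invitation happens there, and Supplementary File 1, to which it refers for detail, is not shown. The Phase II registry is also only an example from a model not yet developed, so it cannot establish that a registry will be an intervention component.

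A second reply is that Phase III describes no selection among overseas-born people aged 40 or older, so invited may be meant to equal eligible. That is a fair reading for intervention sites at follow-up and may make the conflict small there. It says nothing about the other three cells.

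A third reply is that clinical records could capture screening by other providers. This stands. It would be wrong to say the plan necessarily misses usual-care screening, and what remains is the mismatch between the two stated sources.

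None of this removes the main difficulty. If invitations are issued in all four cells, the ratio can be calculated, but only by giving the comparator and the baseline part of the intervention. Operational detail in a supplement would not make that denominator neutral.

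**Conclusion.** The point holds in this form: the primary outcome is worded with two denominators, and the one chosen for calculation depends on the intervention and is described for one of four cells. As a result, the stated rule does not give a like-for-like Difference-in-Differences contrast. This is more than a missing detail, because both possibilities for the undescribed cells lead to a problem.

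The size of any bias cannot be derived from the article. It would depend on the share invited and on how screens are captured in each cell, and neither is given. The sample size of 182, or 543 after clustering, is unaffected by this point alone.

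The conclusion rests on the article as shown and assumes that no invitation procedure for baseline or control sites is set out elsewhere. A reader might go further and infer that people already diagnosed must be excluded, or that one condition must be named as primary. The article does not require either: its outcome counts hypertension and/or diabetes screening and is not limited to new detection. Those are choices of estimand for the investigators.

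**What to change.** Before baseline collection, define the Difference-in-Differences primary outcome as the proportion of eligible adults (overseas-born, 40 or older) with a completed hypertension and/or diabetes screen from any provider within a fixed look-back window. Measure it with the same instrument or record check, on a list or sample drawn up identically, at all 12 sites in both planned cross-sectional rounds. Use this one definition in the outcomes section, Table 2 and the analysis plan, with one stated data source.

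Keep screened over invited as a descriptive measure at intervention sites during follow-up. Base the design weights on eligible adults, not on eligible invitees.

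The cost is modest but not nil. The plan already expects about 100 participants per site, uses the same tools in both rounds, and collects individual covariates such as education, language and comorbidities, so the screening item can be added to that collection. Table 2 lists no survey for Reach, however, so the item or record check is an addition. Control sites will need a list of eligible adults. Self-report brings some recall error, and records some capture error.

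### Reach, the primary impact outcome, is named over eligible adults but calculated over invited adults, and inviting people is part of the model being tested

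*Protocol article*

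**What the plan says.** Under *Outcomes of model implementation*, the Protocol article names Reach as the primary impact outcome and describes it as "the proportion of eligible CALD adults completing hypertension and/or diabetes screening". The RE-AIM summary in the same section also ties Reach to participation of the target population. Later in that section the calculation is fixed: "Reach will be calculated as the number screened divided by the number invited within each site and period", using community registries and screening logs. Table 2, under *Proposed tools for measuring implementation outcomes*, agrees with the calculation and not with the name: "Participation rate: % of individuals invited who actually undergo screening for the target NCDs".

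On who is invited, the section on Phase III says that people from the communities who were "born overseas and are 40 years or older will be registered and invited for the service", and it places this within model implementation at the selected settings. Under *Expected outcomes of Phase II*, a register is one of the examples of what the model might contain: "registry of target population and provision of services can potentially enhance access to and utilization of health services".

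Under *Data analysis plan for the main model*, screening uptake is compared between intervention and control sites over time by Difference-in-Differences with repeated cross-sections. If individual data are pooled with fixed samples per site, the weights are proportional to each site's population of eligible invitees.

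**The concern.** The primary impact outcome has two denominators. The one that will be computed leaves out eligible adults who are never invited, although improving access for such people is the purpose of the model. Because invitation is something the model does, the denominator comes after the intervention. It may move when the model starts, and it need not move in the same way at control sites.

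Wider outreach that brings in people less inclined to attend lowers screened/invited even while more people are screened. Inviting mainly keen members raises it. The estimated effect could then reflect invitation practice as well as the screening of eligible adults. Covariate adjustment cannot recover people who are outside the denominator, and weights built on invitees carry the same restriction. With a single pre-intervention time point, a shift in the denominator cannot be told apart from a change in screening.

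**Working it through.** **The article's own figures.** Under *Cluster size and number of expected participants* the target is 50% rising to 70%, with 80% power and 5% significance. With unpooled variance and a two-sided test, n per group = (1.96 + 0.8416)² × (0.25 + 0.21) / 0.20² = 90.3, so 91 per group and 182 in total, as stated. The design effect is 1 + 99 × 0.02 = 2.98, and 182 × 2.98 = 542.4, about the stated 543. The sample size reproduces and is not in dispute. It confirms that the target effect is 20 percentage points. The section does not say whether the 50% and 70% are over invited or over eligible adults.

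**Relation between the denominators.** Assume that everyone screened was invited. Let r0 and r1 be the proportions of eligible adults screened at baseline and follow-up in intervention sites, and f and g the proportions of eligible adults invited at those times. Then:

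- effect over eligible = r1 − r0
- effect over invited = r1/g − r0/f

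with control sites unchanged on both measures, so that the Difference-in-Differences equals the change in intervention sites. The two expressions are equal when f = g = 1.

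**Putting the target in.** Take r0 = 0.50 and r1 = 0.70 over eligible adults, and g = 1 (everyone invited at follow-up). The effect over invited is 0.70 − 0.50/f. The values of f are assumed.

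| Share invited at baseline, f | Baseline screened/invited | Effect over invited | Effect over eligible |
|---|---|---|---|
| 1.00 | 50.0% | +20.0 points | +20 points |
| 0.90 | 55.6% | +14.4 points | +20 points |
| 0.80 | 62.5% | +7.5 points | +20 points |
| 0.714 | 70.0% | about 0 | +20 points |
| 0.60 | 83.3% | −13.3 points | +20 points |

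**The other direction.** With f = 1 and g = 0.90, the effect over invited is 0.70/0.90 − 0.50 = 0.778 − 0.50 = +27.8 points against a true +20. Likewise, inviting half of the eligible adults and screening 70% of them reports a Reach of 70%, although 0.5 × 0.7 = 35% of eligible adults have been screened.

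**A count example with a large change in coverage.** Assume 200 eligible adults per site. Baseline: 60 invited and 30 screened, which is 30/60 = 50% of invited and 30/200 = 15% of eligible. Follow-up: 180 invited and 81 screened, which is 81/180 = 45% of invited and 81/200 = 40.5% of eligible. The change is −5 points over invited and +25.5 points over eligible.

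**The case against.** The strongest reply is that the text permits a harmless reading. Phase III applies the eligibility rule itself when it says who is registered and invited, and describes no further selection. The analysis section speaks of eligible invitees as if eligible and invited were one group. Reach is to be calculated within each site and period from registries, which presupposes some list in both arms and both rounds. On that reading the first statement is the concept, the second its operational count, and the two coincide. The register is also only an example component of a model not yet developed, and Supplementary File 1, which is not shown, may define the invited set.

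Much of this stands. A reader might infer that control sites will have few or no invitations, or that the planned analysis will show no effect or harm while screening rises. The documents support neither: they give no invitation coverage for any arm or period, and the sign-reversing count example needs coverage to triple, from 30% to 90%, in intervention sites only. A reader might also infer that a single register frozen before activation is needed. That would not suit the repeated cross-sectional design, because it would leave out newcomers and people who turn 40 between rounds.

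The reply does not remove the conflict. The two statements agree only under full invitation at every site in both periods, and nothing shown says that this will be so. The article fixes the calculation itself, so this is a stated rule that disagrees with the named outcome and not a detail left to another document.

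**Conclusion.** The concern holds as an inconsistent definition of the primary impact outcome, with a conditional risk of bias. Reach is named over eligible adults and calculated over invited adults, and invitation is described as an implementation activity, so the intervention can alter the denominator. If coverage differs by arm or period, the Difference-in-Differences can be too small, too large or of the wrong sign.

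The size depends on coverage that the documents do not give. If the 50% to 70% target is taken over eligible adults, with unchanged controls, full invitation at follow-up and no one screened without an invitation, moderate baseline shortfalls matter: at 80% coverage the effect falls from +20 to +7.5 points, and at about 71% it vanishes. If all eligible adults are invited everywhere in both periods, there is no bias and only the wording needs repair. It should be settled before sites are selected, because it determines what the main result means.

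**What to change.** Under *Outcomes of model implementation* and in the Reach row of Table 2, state one primary denominator: all eligible adults (born overseas, aged 40 or older) listed by the same rule at all 12 sites for each period. The list should be compiled independently of programme outreach, so that the model's own invitations do not create it. A fresh list for each period keeps the repeated cross-sectional design intact.

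Under *Data analysis plan for the main model*, base the design weights on the same population instead of on eligible invitees. Report invited/eligible and screened/invited as supporting process measures; their product is screened/eligible when everyone screened was invited, so readers can see which step changed.

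The cost is the same listing work at the six control organisations as at the intervention sites, which is more than a change of wording, and a stated Reach that will be lower than screened/invited wherever invitation is incomplete. The article says that sites have still to be chosen, so the listing rule can be agreed with them at selection.
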